## Null-hypothesis and alternative-hypothesis

Null-hypothesis: biological gender (male or women) does not influence the primary outcome parameter

Alterative-hypotheses: biological gender (male or women) influences the primary outcome parameter

## Study design

Single centre

Main activities during study period:

- Ulnar nerve blockade
- Morphometric measurements of the ulnar nerve via ultrasound
- Evaluation of sensory and motor blockade
- Blood samples for PKs
- Evaluation of ulnar nerve visibility in ultrasound

# Study population

Potential study participants are selected from a subject database of the Department of Clinical Pharmacology according to the inclusion criteria and asked over the phone whether they are basically interested in participating in such a study. If the potential study participants are interested in principle, appointments for an initial interview will then be made via the study secretariat, during which it can then be clarified whether the subject is suitable for inclusion in the study and whether he or she is willing to take part in the present study. The subject is then informed about the procedure, the risks, the compensation for the study and legal aspects (insurance cover, etc.). During this appointment written informed consent is obtained.

## Inclusion criteria for healthy volunteers

- Healthy male and female volunteers
- Healthy, according to the medical history, ECG, vital signs, laboratory results and physical examination as determined by the Investigator/Sub-Investigator
- Signed written informed consent prior to inclusion in the study
- 18-55 years old inclusive
- BMI: 18 to 35 kg/m^2^
- Ability to understand the full nature and purpose of the study, including possible risks and side effects
- Ability to co-operate with the investigator and to comply with the requirements of the entire study
- Availability to volunteer for the entire study duration and willing to adhere to all protocol requirements

## Exclusion criteria for healthy volunteers

- Any clinically relevant abnormalities at ECG (12 leads)
- Any clinically relevant abnormal physical findings
- Any clinically relevant abnormal laboratory values indicative of physical illness
- Ascertained or presumptive hypersensitivity to the active principle and/or formulations ingredients of the study drug
- History of anaphylaxis to drugs or allergic reactions in general, which the investigator considers may affect the outcome of the study
- Relevant history of malignancy, of renal, hepatic, cardiovascular, respiratory, gastrointestinal, musculoskeletal, skin (particularly at the site of drug application), haematological, endocrine or neurological diseases that may interfere with the aim of the study
- Pregnancy
- Any psychiatric illnesses
- Any anticoagulatory or pain-therapy-related drugs (e.g. NSAIDs, opioids) from one week before until the end of the study
- Using other medications during 1 week before the start of IMP application including OTC
- Participation in another clinical study investigating another IMP within 1 month prior to screening
- Blood donations during 4 weeks prior to this study
- History of drug or alcohol abuse
- Other objections to study participation in the opinion of the investigator

## Reason for withdrawal

- At their own request
- Unreliability and/or lack of cooperation
- Signs of clinically relevant illness that might hamper the performance of the study according to the protocol or the evaluation of safety
- Alcohol or drug abuse
- Occurrence of adverse events (signs and symptoms) or inter-current diseases which the investigator deems to be unacceptable
- Other objections to participate in the study in the opinion of the investigator

# Study drug

## Ropivacaine

Ropivacaine is an amino-amide sodium channel blocker and labelled for nerve blockade and neuraxial anaesthesia.

Ropivacaine is labelled for surgical anaesthesia and acute pain management for the following indications:

- Peripheral nerve blockade
- Surgical infiltration
- Epidural block for surgery including Caesarean section

### Pharmacokinetic data

Formula: C_17_H_26_N_2_O
Chemical name: (S)-1-Propyl-2',6'-dimethyl-2-piperidylcarboxyanilid
Molecular mass: 274.408 g·mol^−1^
Protein binding: 94% (mainly to α_1_-acid glycoprotein)
Metabolism: Hepatic (CYP1A2-mediated)
Elimination half-life: 1.6 - 6 hours (dependent on administration route)
Excretion: Renal (86 %)

### Complete description of indications, contraindications, undesirable and general side effects

See Appendix 1

# Study protocol

Upon signature of the informed consent form and provided that the inclusion/exclusion criteria are fulfilled, subjects will be enrolled in the study.

Overall duration of the study for each individual subject is planned to be two weeks.

## Screening visit (day -14 to day-1)

Prior to inclusion subjects will be informed about the objective and the procedures of the study and about the risks involved. In- and exclusion-criteria, demographic data including underlying disease will be assessed. Each enrolled healthy volunteer will be scheduled to undergo a general physical examination including anamnesis, determination of BMI, drawing blood for laboratory screening tests (including complete blood count, blood coagulation tests, serum electrolytes, creatinine, γ-GT, AST, ALT, CK, total protein, total bilirubin and virology (HBsAg, HBcAg, HCV, HIV-will be accepted if not older than 6 months), Covid-19 PCR test (optional- according to currently valid rules of access to the hospital and/or national regulations), vital signs recording (blood pressure (BP) and heart rate (HR) after 5 minutes rest in supine position) and electrocardiogram (ECG). In addition, urine analyses will be performed. For female participants, an urine pregnancy rapid test will be performed.

## Study day

In the morning of the study day volunteers will be admitted to the clinical research ward which they will not leave until return of sensory and motor function (definitions see below).

The volunteers will receive a plastic cannula (Venflon®) with a switch-valve inserted into an antecubital vein for iv. administration of emergency drugs (in case of hypotension or bradycardia). Thereafter the nerve blocks will be performed as described elsewhere. Each volunteer will receive one ultrasound guided ulnar nerve block on the non-dominant arm.

The sensory evaluation of the nerve block will be assessed with Pinprick testing. The motor evaluation of the nerve block will be assessed by adduction of the thumb.

## Final examination

The final visit (evaluation of ulnar nerve function and puncture site of the nerve block) will be performed up to 7 days after the study via a telephone interview. The volunteers will be called up to study centre in cases of abnormalities.

# METHODS

## Nerve blocks

All ulnar nerve blocks will be performed with ultrasound guidance and a high frequent linear ultrasound probe (8-15 MHz). A transportable ultrasound machine will be used (SonoSite™ X-Port, Bothell, WA, USA). Sterile conditions will be achieved by sterile preparation of the nerve block puncture area and the use of a sterile ultrasound probe cover. Three ml ropivacaine 7.5 mg/ml (= 22.5 mg) for a single peripheral nerve block will provide an effective and selective nerve block.

## Sensory assessment of blockade

The sensory evaluation of the nerve blocks will be assessed before and after blockade with Pinprick Testing (time intervals see below).

## Motor assessment of blockade

Evaluation of motor blockade of the nerve blocks will be assessed before and after blockade according to a four-point scoring system (time intervals see below).

## Definition of onset times

### Sensory blockade

Time from performance of blockade (injection of LA with or without dexamethasone) to Pinprick = 0 in 4 from 5 predefined sensory areas of the ulnar nerve.

### Motor blockade

Time from performance of blockade (injection of LA with or without dexamethasone) to motor score = 0

## Definition of duration of blockade

### Sensory blockade

Time from Pinprick = 0 to Pinprick = 80

### Motor blockade

Time from motor score = 0 to motor score = 1

## Time points

Baseline, 2, 4, 6, 8, 10, 15, 20, 30, 60 min after the block, and then every 30 min until complete recovery.

## Blinding

-

## Power Analysis

A previous study with ropivacaine 0.75% for ulnar nerve blockade showed a duration of sensory blockade of 350 min with the largest SD of 54 minutes.^2^ We expect a true difference of approximately 35 minutes (10%). Assuming a true difference in means between the test and the reference group of 35 minutes, a pooled standard deviation of 54 minutes, the study would require a sample size of 38 for each group (i.e. a total sample size of 76, assuming equal group sizes), to achieve a power of 80% and a level of significance of 5%, for declaring that the duration of block in one biological gender group is longer than in the other biological gender group at a 5 minutes margin of superiority (assuming that a longer duration is desirable). For nonparametric analysis, the sample size is increased by 15% to 90 subjects.

After 2 x 12 cases, we perform an interim analysis for re-evaluation of the initially calculated number of 90 cases (power = 80%, level of significance = 5%). Based on the results of the primary outcome parameter after interim-analysis, a power analysis (to achieve a power of 80% and a level of significance of 5%) to find a nominal difference of 10 to 15% will be performed to determine the number of additional study cases which will be investigated.

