| POWER ANALYSIS | A previous study with ropivacaine 0.75% for ulnar nerve blockade showed a duration of sensory blockade of 350 min with the largest SD of 54 minutes.^2^ We expect a true difference of approximately 35 minutes (10%). Assuming a true difference in means between the study groups of 35 minutes, a pooled standard deviation of 54 minutes, the study would require a sample size of 38 for each group (i.e. a total sample size of 76, assuming equal group sizes), to achieve a power of 80% and a level of significance of 5%. For nonparametric analysis, the sample size is increased by 15% to *90* subjects.  After 2 x 12 cases, we perform an interim-analysis to re-evaluate the number of initially calculated subjects. A subsequent power-analysis will be performed to determine the definitive number of study cases. We intend to achieve a power of 80% and a level of significance of 5% to find a nominal difference of 10 to 15%.  Interim analyses and sample size calculations will be conducted using the O’Brien-Fleming alpha spending function for test boundaries in PASS and NCSS software (NCSS Inc., Kaysville UT.) |
| STATISTICAL METHODOLOGY | Pharmacodynamic data analysis: The primary outcome is duration of sensory block. Secondary outcomes include onset of sensory block, onset and duration of motor block.  Data will be presented as mean (SD), median [interquartiles] and count (%) and analysed using unpaired two-sided Student *t-*, Mann-Whitney *U-*, log-rank and Fisher exact statistics. The primary outcome will be analysed using unpaired Student *t-*, Mann-Whitney *U-* or log-rank statistics as appropriate. Secondary analyses will include mixed effects linear models to adjust for subject and baseline characteristics and for repeated measures in subjects as random intercepts.  Pharmacokinetic data analysis: Secondary outcomes, including parameters such as C_max_, t_max_and AUC will be estimated and analysed using statistics as listed above.  Morphometric data analysis: Differences between grey scales of nerves and nerve visibility (differences between nerves and surrounding tissue) and differences in the Vienna Scoring System will be compared using unpaired two-sided Student *t-* or Mann-Whitney *U-* statistics as appropriate. Mixed effects linear models will be performed to determine the correlation of nerve visibility with morphometric variables. |

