# STATISTICAL / ANALYSIS SECTION

## Sample size calculation

A previous study with ropivacaine 0.75% for ulnar nerve blockade showed a duration of sensory blockade of 350 min with the largest SD of 54 minutes.^2^ Assuming a nominal difference in means between the study groups of 35 minutes, a pooled standard deviation of 54 minutes, the study would require a sample size of 39 for each group (i.e. a total sample size of 78, assuming equal group sizes), to achieve a power of 80% and a level of significance of 5%. To enable nonparametric analysis, the sample size is increased by 15% to 90 subjects. For a larger nominal 15% difference, the total sample size is reduced to 42 subjects.

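### The METHODS power analysis attaches a 5-minute superiority margin to a sample size that was calculated without one

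*Protocol*

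**What the plan says.** The protocol gives the sample-size calculation three times.

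- **METHODS, Power Analysis.** It begins "Assuming a true difference in means between the test and the reference group of 35 minutes", takes "a pooled standard deviation of 54 minutes", and arrives at 38 per group (76 in total) "to achieve a power of 80% and a level of significance of 5%, for declaring" one sex's block longer than the other's "at a 5 minutes margin of superiority (assuming that a longer duration is desirable"). The total is then raised by 15% to 90 for nonparametric analysis.
- **Synopsis, Power Analysis.** Same difference, SD, power and level, with no margin: "the study would require a sample size of 38 for each group", again raised to 90.
- **Statistical / Analysis Section, Sample size calculation.** Same inputs, with no margin: "the study would require a sample size of 39 for each group (i.e. a total sample size of 78", also raised by 15% to 90.

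The section on the hypotheses has no margin and no direction: "Null-hypothesis: biological gender (male or women) does not influence the primary outcome parameter". The Synopsis hypothesis says the same. The analysis text in the Synopsis, in METHODS and in the Statistical / Analysis Section plans two-sided t-tests, with rank, log-rank and Fisher tests alongside. None of these places mentions 5 minutes, a test group, a reference group or a preferred direction.

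**The concern.** A test of superiority by a margin asks for more than a test of no difference. If the true difference is 35 min and the margin is 5 min, only 30 min separates the truth from the boundary of the null hypothesis, so the same sample gives less power. A sample size that fits the zero-margin test therefore cannot carry the same 80% for the margin test, and the METHODS paragraph claims that it does.

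The wording also does not fit the study. Both sexes receive the same drug, volume and dose, so neither group is a test or a reference, and the protocol gives no reason elsewhere to prefer a longer block in either sex.

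The practical stake is the re-estimation after 2 x 12 volunteers, which repeats the power analysis to set the final number. Whoever does it needs to know the criterion: for 35 min and SD 54 min, the two-sided requirement before the 15% uplift is 39 per group without the margin and 52 with it.

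**Working it through.** **Inputs, all from the protocol.** Difference 35 min, SD 54 min, power 80%, level 5%, margin 5 min, equal groups, planned 45 per group. The METHODS paragraph does not state the sidedness of its calculation, so both readings are shown.

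**1. Reproduce the stated 38 and 39 (no margin, two-sided 5%).**
Normal approximation: n per group = 2(z_α + z_β)² SD² / Δ².
(1.960 + 0.842)² = 7.849, so n = 2 × 7.849 × 54² / 35² = 2 × 7.849 × 2916 / 1225 = 37.4, rounded up to **38**.
Exact t-test (noncentral t): power is 79.6% at 38 per group and 80.7% at 39, so the requirement is **39**.
Both stated figures are thus zero-margin, two-sided results; they differ only in the approximation used.

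**2. Put the margin in.** Effective distance = 35 − 5 = 30 min. The two-sided 5% reading means that the 95% confidence interval lies wholly beyond 5 min, which has the same power as one-sided 2.5%.

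- Two-sided 5%: n = 2 × 7.849 × 2916 / 900 = 50.9, so 51 by normal approximation; the t-test needs **52**.
- One-sided 5%: (1.645 + 0.842)² = 6.183, so n = 2 × 6.183 × 2916 / 900 = 40.1, so **41**; the t-test also gives 41.

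**3. Look for any reading that gives 38 with a margin.** Adding the margin instead (35 + 5 = 40 min) gives 29 to 30 per group two-sided and 23 to 24 one-sided. No use of the margin returns 38.

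**4. Power by t-test.** SE = 54√(2/n), noncentrality = distance / SE.
At 38 per group, SE = 12.39 min and 30 / 12.39 = 2.42. At 45 per group, SE = 11.38 min; 30 / 11.38 = 2.64 and 35 / 11.38 = 3.07.

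| Criterion | 38 per group | 45 per group | n per group for 80% |
|---|---|---|---|
| No margin, two-sided 5% | 79.6% | 86.0% | 39 |
| 5-min margin, two-sided 5% | 66.6% | 74.1% | 52 |
| 5-min margin, one-sided 5% | 77.5% | 83.4% | 41 |

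The normal approximation puts the two margin figures at 38 per group at 67.8% and 78.1%.

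**5. Where the two criteria would disagree.** At 45 per group with SD 54, the two-sided t-test rejects no difference when the observed difference exceeds 1.987 × 11.38 = 22.6 min. Clearing the margin would need 22.6 + 5 = 27.6 min. If the true difference is 35 min, a result falls between the two with probability of about 86.0% − 74.1% = 12 percentage points.

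**6. The 15% uplift.** 76 × 1.15 = 87.4, or 88 rounded up. 78 × 1.15 = 89.7, or 90. The 90 stated in all three places follows from 39 per group.

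**The case against.** The strongest reply is that the margin clause is stray wording with no operative force. It appears once, in a sample-size rationale, and no hypothesis or analysis section tests against 5 minutes. That stands. A reader might infer that the protocol sets two rival success criteria for its primary outcome. The documents do not support this: the hypothesis and analysis sections carry one criterion, no difference tested two-sided, and the disagreement in step 5 arises only if someone treats the rationale as the decision rule.

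A reader might also infer that the calculation is for a test in one fixed direction. The text speaks of "declaring that the duration of block in one biological gender group is longer than in the other biological gender group" and does not say which sex, which is compatible with a two-sided test. Only the test and reference labels and the preference for a longer block sound directional.

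Nor do the documents support the inference that the study is too small. The planned 45 per group gives 86.0% for the hypothesis actually stated, and 83.4% even with the margin at one-sided 5%. It falls below 80% only if the margin is combined with two-sided 5%. The 90 is also provisional, since the number is to be re-determined after the interim analysis for a 10 to 15% difference with no margin mentioned.

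Finally, 38 against 39 is normal approximation against t-test, worth 0.4 points of power (79.6% against 80%), and recruiting 90 rather than 88 errs on the safe side. Both are side points.

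What the reply does not remove is that the sentence as written claims 80% power for a criterion that 38 per group does not meet under either usual level.

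**Conclusion.** The power stated in the METHODS paragraph is wrong for the criterion stated with it. At 38 per group the shortfall is about 13 points at two-sided 5% (66.6% against 80%) and 2.5 points at one-sided 5% (77.5%). The two-sided figure is the more relevant, because the planned t-tests are two-sided and one-sided testing is not proposed anywhere in the protocol. The clause also contradicts the non-directional hypothesis.

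This should be fixed, but it does not threaten the design: the defect lies in the stated criterion and its power, not in the planned 90. The figures assume a difference of 35 min, a common SD of 54 min, normal data and a fixed-design t-test. They make no allowance for the interim analysis with O'Brien-Fleming boundaries or for the efficiency of a rank test, which the 15% uplift is meant to cover.

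**What to change.** Delete the 5-minute margin, the test and reference labels and the statement that longer is desirable from the Power Analysis under METHODS. Give the same calculation there, in the Synopsis and in the Sample size calculation: two-sided 5% t-test of no difference, difference 35 min, SD 54 min, 80% power, 39 per group (78 in total), raised by 15% to 90. The interim re-estimation should refer to that criterion.

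The cost is wording only: no planned number, test or hypothesis changes.

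If the sponsor does intend a 5-minute margin, deletion is not the remedy. The hypothesis and the primary test must then state the margin and its sidedness, and the power at 45 per group must be restated accordingly: about 74% at two-sided 5% or 83% at one-sided 5%, before any allowance for the interim analysis. On the two-sided reading, 90 would no longer meet the 80% target.

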## Statistical Analysis

Pharmacodynamic data analysis: The primary outcome is duration of sensory block. Secondary outcomes include onset of sensory block, onset and duration of motor block.
Data will be presented as mean (SD), median [interquartiles] and count (%) and analysed using unpaired two-sided Student *t-*, Mann-Whitney *U-*, log-rank and Fisher exact statistics. Mixed effects linear models will be used to adjust for subject characteristics.

Pharmacokinetic data analysis: Secondary outcomes, including parameters such as C_max_, t_max_and AUC will be estimated and analysed using statistics as listed above.

Morphometric data analysis: Differences between grey scales of nerves and nerve visibility (differences between nerves and surrounding tissue) and differences in the Vienna Scoring System will be compared using unpaired two-sided Student *t-* or Mann-Whitney *U-* statistics as appropriate. Mixed effects linear models will be performed to determine the correlation of nerve visibility with morphometric variables.

# Drug Storage

All study drugs will be stored at room-temperature (20°C-25°C), protected from light, at the Department of Clinical Pharmacology and will be protected against unauthorized access.

Records of the investigational product's delivery to the trial site, the inventory at the site, the use by each subject, and the disposition of unused product will be kept by an experienced research nurse. These records will include dates, quantities, batch/serial numbers, expiration dates, and the unique code numbers assigned to the investigational product and trial subjects.

# Labelling

## Subject identification

Subject numbers 001 - 090 will be used in a consecutive order. Subjects withdrawn from the study will retain their identification code. New replacement subjects enrolled will be assigned a number equal to the study number of the withdrawn subject plus 100 units: e.g. subject 001 will be replaced by the subject 101, subject 02 by subject 102 Sample identification

Each sample will be clearly and unequivocally identified with a label resistant to the storage temperature and containing the following information:

Abbreviated name of the study (Gender_PNB)

Subject number (001-090)

Scheduled time of sampling (hh:min)

Content (P1 / P2).

# Life style restrictions

The following restrictions will apply during the study:

- Intake of concomitant medication except in case of emergency or treatment of AEs
- Intake of excessive alcohol

# Documentation

The following documents must be available in the Investigator’s study file prior to the enrolment of any subject:

- Copy of the positive vote from the Ethics Committee;
- A list of members of the Ethics Committee in accordance with local regulations;
- Notification to local and national regulatory authority;
- Sample of the consent form and subject information to be used;

Data of screening examination will first be kept in separate subject files (source data files) and will be entered into the CRF only if the subject is eligible for trial participation and the data were verified by an investigator.

The subjects will be monitored through the course of the trial and all findings will be recorded.

The records should include the study number, the taking of consent, visit dates of the patient, medical history or examinations administered, laboratory results, concomitant treatment and sample collection times for diagnostic as well as pharmacokinetic samples, any adverse events encountered, and other notes as appropriate.

AEs as reported by the patients will be recorded on separate forms as source data in German or English language and will be transcribed into the CRF after translation in English language. A physician will do the judgement according to the criteria of the ”Adverse Events” page.

Data of medical measurement without print-outs (vital signs, time of trial activities, i.e. time of sampling, administration) performed during the trial will be recorded on worksheets and will be handled as source data. Clinical laboratory parameters will be provided in laboratory print-outs which were signed and dated by the investigator. Comments on all clinically significant abnormal values should be given by the investigator. Data which are subject to the data protection law (i.e. name, address) will not be entered into the CRF.

For error corrections in source data the investigator or an authorized clinical staff member will cross out the part to be corrected (no correction fluid!) with one line, so that the incorrect data is still readable, and then entering the correct data, initialling and dating the change.

All correspondence (e.g. with Ethics Committee) relating to this clinical trial should be kept in appropriate file folders. Records of subjects, source documents, drug inventory sheet and Informed Consents pertaining to the trial must be kept on the Investigator’s File. Records must be retained according to guidelines governing the conduct of the trial.

According to the European Community record retention is required for 15 years.

If the investigator moves, withdraws from an investigation or retires, the responsibility for maintaining the records may be transferred to another person who will accept the responsibility.

